### Fluid intervention in liver resection

Recently, the authors completed a multicentre randomized double-blind controlled multicentre study of Plasmalyte vs. Hartmann's solution in patients receiving liver resection. Participants were randomized to Plasmalyte or Hartmann's solution for intraoperative fluid intervention. Primary outcome: base-excess immediately after surgery. Secondary outcomes: lactate levels, strong-ion-difference (SID), total weak acids, net-unmeasured-ions, changes in liver enzymes, perioperative complications and duration of hospital stay. Results: 60 participants were recruited from 4 tertiary-level hospitals. Both groups were matched according to baseline characteristics, extent of resection, and surgery duration. There were no differences in the volume of trial fluid used, perioperative fluid balance, or urine output. Plasmalyte was not inferior to Hartmann's for the primary endpoint. Plasmalyte base-excess was 0.8mmol/L greater (95%CI: -0.4 to 2.0;P=0.18). This was associated with hyperchloraemia (Difference 1.7mmol/L, 95%CI: 0.2 to 3.2mmol/L, p=0.03) and hyperlactaemia (Difference 0.8mmol/L, 95%CI: 0.2 to 1.3mmol/L;P=0.01) in the Hartmann's group. In the Hartmann's group 23 patients (77%) had a lactate above the reference range compared to 14 patients (47%) in the Plasmalyte group, P=0.02. Complications were more frequent in the Hartmann's Group (56% vs. 20%, 95%CI: 1.3 to 6.1;P=0.007). Median length of hospital stay: 5.9 days vs. 7.8 days (P=0.041) favouring Plasmalyte group.

**The SPLIT Study: Saline (0.9%) vs. Plasma-Lyte® 148 Fluid Intervention Trial in Major Surgery Patients, Version 3, 1st Oct 2014**

Conclusion: For patients undergoing liver resection use of Plasmalyte solution resulted in improved acid base haemostasis, less hyperlactaemia, reduced perioperative complications and a shorter length of hospital stay compared to patients receiving Hartmann's solution.

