## OBJECTIVES

The overall objective of this study is to establish the feasibility, safety and relative biochemical and physiological efficacy of using saline (0.9%) vs. Plasmalyte solution as the primary fluids in adult major surgery patients.

The choice of non-crystalloid fluid intervention such as colloids, or any other blood product e.g. red blood cells, platelets, cryoprecipitate, frozen plasma, bicarbonate, dextrose etc. will be entirely at the discretion of the all clinicians caring for the patients

Specifically, we aim to establish the effect of saline (0.9%) and Plasmalyte solution on:

1. The development of acute kidney injury in hospital
2. The development of biochemical and acid-base derangements
3. The development of postoperative complications
4. Requirements for renal replacement therapy
5. Requirements for mechanical ventilation
6. Hospital length of stay
7. Hospital mortality

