### 1.17.2 Primary outcome measure

The primary outcome measure will be the proportion of patients with either acute kidney injury or failure based on creatinine levels in accordance with RIFLE-criteria during the index hospital admission.

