### 1.17.3 Secondary outcome measures

Secondary outcomes will be

- the incidence of acute kidney injury based on creatinine according to risk, injury, failure, loss, end-stage (RIFLE) classification in the first 3 days hours after surgery,
- the increase between baseline and peak chloride levels in the first 3 days after surgery
- the development of metabolic acidosis (defined as a base deficit > 2 mEq/L or a bicarbonate level <20 mmol/L) in the first 3 days after surgery
- the development of acidemia defined as a pH <7.3 in the first 3 days after surgery
- Postoperative complications
- Need for and duration of renal replacement therapy,
- Proportion of patients requiring mechanical ventilation
- Need for ICU admission
- ICU and hospital length of stay, and
- ICU and in-hospital mortality

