## DATA MANAGEMENT

### 1.21 Data collection methods

The demographic, biochemical, and outcome data used in this study are already collected by the Austin Hospital for administrative and quality assurance purposes.

Any ICU data are similarly collected and already provided to the Australian and New Zealand Intensive Care Society Centre for Outcome and Resource Evaluation as part of a government-funded bi-national quality assurance programme.

The only data used in this study which are not routinely collected for quality assurance purposes are the daily volume of study fluid administered as fluid boluses and the data relating to renal outcomes. These data will be collected by the Principle investigators or trained Research Co-ordinators.

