## **SAFETY CONSIDERATIONS**

### **1.24 Adverse Events and Other Safety Aspects**

Safety will be assessed throughout the study. As part of normal hospital care for all patients undergoing surgery at Austin Hospital, a complete baseline profile of each subject will be established by the treating surgical unit through medical history, clinical laboratory values, vital signs, physical assessments, and ECGs. During the course of the study, surgical and anaesthesia care, including vital signs, complete and targeted physical assessments, laboratory tests, and ECGs will be performed in accordance with normal hospital protocols. **There will be no deviation from standard care at any time point.**

All medical and surgical changes from baseline will be monitored throughout the study by the treating units and appropriate interventions will be taken accordingly.

The documentation of all adverse events specifically related to fluid intervention will begin at the time of first Trial Fluid administration and continue through to hospital discharge of all subjects involved in the study.

Data will be recorded in the CRF and will include a description of the event, date of onset, onset status (onset before/after the first dose of study medication), end of the event, severity, course of events, SAE, seriousness criteria, action with respect to study medication, treatment required, related to Trial Fluid and outcome of the event. AEs will be recorded and tabulated using the Common Terminology Criteria for Adverse Events (NCI-CTCAE) Version 4.0.

Severity of events will be determined by the Principal Investigators.

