### 1.30 Analysis plan

A complete description of the statistical analyses will be specified in a statistical analyses plan, finalised prior to completion of the study.

All analyses will be conducted on an intention-to-treat basis.

The primary analyses will be unadjusted analyses in which binary outcomes will be compared using relative risks with 95% confidence intervals and chi square tests and continuous outcomes will be compared with the use of mean

**The SPLIT Study: Saline (0.9%) vs. Plasma-Lyte® 148 Fluid Intervention  
Trial in Major Surgery Patients, Version 3, 1st Oct 2014**

differences and un-paired T-tests assuming that normality assumptions are met. If normality assumptions are not met then we plan to attempt simple data transformation, such as a logarithm transformation, and if this fails to proceed to a Mann-Whitney rank based test. Adjusted analyses will be performed using Poisson regression for binary outcomes and linear regression for continuous outcomes. Baseline covariates will include age, gender, elective vs. emergency surgery, surgical specialty of admission, type of operation, and baseline serum creatinine level. Survival times will be compared using log-rank tests and presented as Kaplan-Meier curves.

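### Log-rank tests and Kaplan-Meier curves are planned for survival times, but deaths are captured only in hospital; if live discharge is censored, a difference in length of stay can appear as a difference in mortality

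*Protocol*

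**What the plan says.** Protocol section 1.30 (Analysis plan), repeated under Statistical Methods in the Study Synopsis, fixes the method: "Survival times will be compared using log-rank tests and presented as Kaplan-Meier curves". It gives no time origin, horizon or rule for patients who leave hospital alive. The full description of the analyses is deferred to a statistical analysis plan.

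Section 1.17.3 lists no time-to-event outcome. Its only mortality item is "ICU and in-hospital mortality", and the corresponding aim under Objectives is "Hospital mortality". The item just before it in section 1.17.3 is "ICU and hospital length of stay, and", so length of stay is an outcome in its own right.

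The primary outcome is assessed "during the index hospital admission" (section 1.17.2). Section 1.21 says that the demographic, biochemical and outcome data "are already collected by the Austin Hospital for administrative and quality assurance purposes". No contact or linkage after discharge is described.

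Section 1.30 also plans relative risks with 95% confidence intervals and chi-square tests for binary outcomes, by intention to treat. In-hospital death falls under that rule.

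**The concern.** With deaths recorded only in hospital, the natural reading of survival time is time to in-hospital death. Standard software then treats a patient discharged alive as censored on the day of discharge. Kaplan-Meier and log-rank need censored patients to carry the same future risk as those still under observation. Patients discharged alive are at clearly lower risk, and discharge also rules out the event being counted, so it is a competing event.

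Two distortions follow. First, the Kaplan-Meier curve rises well above the true proportion dying, because each late death is divided by a small and increasingly sick group of remaining inpatients. Second, if one fluid shortens stay without changing who dies or when, that arm's risk set shrinks faster and the arm looks worse.

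The protocol takes a stay difference seriously. It reports one from its own group's earlier liver-resection trial: "Median length of hospital stay: 5.9 days vs. 7.8 days (P=0.041) favouring Plasmalyte group". The comparator there was Hartmann's solution, so this illustrates a plausible size and is not a forecast for saline. The present study is a pilot meant to supply safety data for a larger trial, so a spurious mortality signal against the arm that recovers faster could mislead the next design.

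**Working it through.** The plan gives no expected mortality, death-time or overall stay figure, so there is no plan figure to reproduce on this point.

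**Inputs from the protocol.** 1000 patients per group (section 1.10), and 7.8 vs 5.9 days as an illustrative stay difference (Fluid intervention in liver resection).

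**Assumptions.** In-hospital mortality of 1-4%, and the distributions of stay and time to death. None of these is in the protocol.

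**Step 1: same deaths and death times in both arms, only survivors' stay differs, live discharge censored.** Stay and death times were log-normal (log SD 0.8 and 0.9), median time to death 7 or 12 days, 2000 replicates per setting, two-sided 5% log-rank test. Stays are medians.

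| Median stay (days) | Mortality | Log-rank rejection | Apparent hazard ratio, shorter-stay arm |
|---|---|---|---|
| 5.9 vs 5.9 | 1-4% | 5-6% | about 1.0 |
| 6.5 vs 5.9 | 1-4% | 6-10% | 1.12-1.16 |
| 7.8 vs 5.9 | 1% | 13-18% | not given (unstable) |
| 7.8 vs 5.9 | 2% | 18-27% | 1.37-1.51 |
| 7.8 vs 5.9 | 4% | 27-43% | 1.35-1.48 |

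**Step 2: other distributions.** With gamma distributions, stays given as means and 1-3% mortality, rejection was 13-32% for 7 vs 6 days and 27-73% for 7.8 vs 5.9 days, all or nearly all against the shorter-stay arm. Together with step 1, the span for 7.8 vs 5.9 days is 13-73%. These are not hard limits. When deaths were also allowed to come early (mean 5 days), rejection for 7 vs 6 days fell as low as 7%. In the gamma runs the Kaplan-Meier reading at day 14 was about 2 to 6 times the true value.

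**Step 3: same deaths, other analyses.** In the step 1 runs, keeping live discharges at risk to a common horizon, or comparing the proportion dying in hospital, gave 4.3-6.4% rejection whatever the stay difference.

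**Step 4: same daily death hazard h in both arms, only the discharge rate d differs.** With constant hazards, d = ln 2 / median stay, and the proportion dying in hospital is h / (h + d).

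- Discharge rates: 0.6931 / 7.8 = 0.0889 and 0.6931 / 5.9 = 0.1175 per day.
- h = 0.0025: 0.0025 / 0.0914 = 2.7% and 0.0025 / 0.1200 = 2.1%.
- h = 0.005: 0.005 / 0.0939 = 5.3% and 0.005 / 0.1225 = 4.1%.

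Simulated log-rank rejection is about 4.6%, so there is no inflation. Here the in-hospital proportion moves instead, and its test rejects in 15% and 25% of trials.

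The curve still misleads. Kaplan-Meier at day 14 estimates 1 - exp(-h × 14). For h = 0.0025 this is 1 - exp(-0.035) = 3.4% in both arms. The true cumulative incidence is [h / (h + d)] × [1 - exp(-(h + d) × 14)]. In the longer-stay arm this is 0.0274 × (1 - exp(-1.279)) = 0.0274 × 0.722 = 2.0%.

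**The case against.** The strongest reply is that the protocol nowhere says live discharge is censored. Section 1.30 leaves the full description to a statistical analysis plan, which could keep discharged patients at risk to a fixed day or use a competing-risk method. Step 3 shows the test is then sound. This stands, and the point must be conditional. It does not remove the point, because the protocol commits to a named method and describes no data after discharge with which its default form would be valid.

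A reader might infer from section 1.24 that vital status ends at discharge, since its documentation is to "continue through to hospital discharge of all subjects involved in the study". That sentence governs adverse events related to fluid intervention. The absence of later follow-up rests on the outcome list and the data sources.

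A reader might also infer that a stay difference is bound to produce a false mortality finding. Step 4 shows otherwise: with an equal daily death hazard the log-rank test keeps its size. Even with identical deaths, rejection ran from close to nominal to well over half of trials, depending on assumed distributions.

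Finally, an unaffected comparison of in-hospital death is already planned and would sit beside the survival analysis. Mortality is secondary, and the kidney-injury result is untouched. All of this stands and limits the consequence.

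**Conclusion.** The concern holds in conditional form. The protocol names log-rank and Kaplan-Meier for survival times, while its only deaths are those in ICU or hospital, and it does not say what happens at live discharge. Under the default handling the censoring is informative and the curves overstate mortality. A difference in stay can then appear as a mortality difference against the arm discharged sooner.

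With identical deaths and death times, 1000 per arm and assumed mortality of 1-4%, the false-positive rate of the 5% test is roughly 13-32% for 7 vs 6 days and 13-73% for 7.8 vs 5.9 days. It is lower if deaths come early, and nominal if the daily death hazard is equal in the two arms. The documents do not support saying that such a bias will occur, or that the protocol prescribes censoring at discharge. The wording should be corrected, but the primary analysis is not affected.

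**What to change.** In section 1.30, the synopsis and the statistical analysis plan:

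1. Name the already planned relative risk of in-hospital death, with its 95% confidence interval and all patients in the denominator, as the mortality comparison.
2. Delete the log-rank and Kaplan-Meier sentence for mortality. If a display over time is wanted, replace it with the cumulative incidence of in-hospital death with live discharge as a competing event (Aalen-Johansen estimate, Gray's test). Keeping live discharges at risk to a common horizon is equivalent. State the time origin and the horizon.

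This is a wording change that uses standard software and needs no new data. There is one small downside. As step 4 shows, the in-hospital proportion can itself shift with length of stay, so it should be reported and read as in-hospital death only. A comparison free of that limit would need vital status to a fixed day for every patient, which means data the protocol does not now plan to collect.

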### 1.31 Sub-groups

There will be the following subgroups:

- Patients undergoing abdominal surgery
- Patients undergoing vascular surgery
- Patients undergoing thoracic surgery
- Patients undergoing other surgeries (orthopaedics, urology etc.)
- Patients undergoing emergency surgery

### 1.32 Randomization process

Participants will be assigned to one of two groups, (Saline or Plasmalyte) using a random number allocation system (<http://www.randomization.com>).

### 1.33 2 Blinding

This is a double-blinded clinical trial. Blinding of all Trial fluids will be done by Baxter Healthcare Australia (BHA). BHA will compound the products in a strictly aseptic process. The shelf life of the solutions prepared will be set at 360 days, when stored below 25°C. Fluids will be prepared in 1 L clear plastic fluid container flasks (the exact same packaging that the fluids are normally prepared in). In order to differentiate between the three trial solutions, BHA will assign the Fluids with a unique code and batch number (Figure 1). Baxter will reveal the batch numbers corresponding to Fluids at the end of the data collection period. Each group will be assigned to a batch number, which matches the specific solution that the patient will be randomized to.

Importantly, study participants, and all involved in their medical and surgical treatment: surgeons, anaesthetists, anaesthesia nurses and all clinical staff involved in the care of each participant will be blinded to treatment allocation.

**Figure 1. Labelling on blinded trial fluid bag showing label information including batch numbers**

**The SPLIT Study: Saline (0.9%) vs. Plasma-Lyte® 148 Fluid Intervention Trial in Major Surgery Patients, Version 3, 1st Oct 2014**

[figure not shown]

## STUDY BUDGET

The **SPLIT Study**: **S**aline (0.9%) vs. **P**lasma-**L**yte® 148 Fluid **I**ntervention  
**T**rial in Major Surgery Patients, Version 3, 1st Oct 2014

### 1.34 Detailed budget

| Item                                                                                                                                                                                                                                                                                         | Year 1                                       |
|----------------------------------------------------------------------------------------------------------------------------------------------------------------------------------------------------------------------------------------------------------------------------------------------|----------------------------------------------|
| Compounding of trial fluid solutions:
Cost: \$1.16 per litre for Saline (0.9%)
Cost: \$1.77 per litre Plasmalyte
Assuming 1000 patients each group each requiring 10L fluid each
Total Fluids:
Plasmalyte: 10 000 Litres
Saline (0.9%): 10 000 Litres | 

\$17 700
\$11 600 |
| Computer consumables (printing, paper, ink)                                                                                                                                                                                                                                           | \$1000                                       |
| Professional statistical consultation                                                                                                                                                                                                                                                 | \$3000                                       |
| Application to TGA for CTN                                                                                                                                                                                                                                                            | \$300                                        |
| Total (AUD)                                                                                                                                                                                                                                                                           | \$ 33,600                             |

### 1.35 Dispensing and storage costs

There will be no additional costs incurred for the dispensing of the Trial fluids by Austin Hospital pharmacy beyond that which is already part of normal dispensing practices. [name] will be responsible for the supply of fluids to the allocated areas in theatres, intensive care and the surgical wards.

Baxter Healthcare will deliver all fluids to Austin Hospital as part of normal Hospital protocols and fluid will be stored in Austin Stores in accordance with normal pharmacy practices.

Baxter Healthcare will be responsible for the cost of compounding of all the trial fluids.

## **STUDY ADMINISTRATION STRUCTURE**

### **1.36 Department of Anaesthesia & Intensive Care responsibilities**

- Overall management of the study will be by both the Department of Anaesthesia and Intensive Care at Austin Hospital
- Both departments will be involved in the case report form design and production
- Both departments will provide assistance for training for Research Co-ordinators and study team if necessary
- Co-ordination of delivery of study fluids will be under the care of [name], Director of Pharmacy at Austin Hospital
- Study database set-up and co-ordination of data entry will be conducted by all principle investigators

### **1.37 Data management responsibilities**

- Data queries
- Data analysis

### **1.38 Management committee responsibilities**

- The Principle Investigators will liaise with all surgical units in the introduction of this trial. In addition, all ward nursing staff, resident medical officers and clinicians caring for these patients will be informed and educated about the study rationale and design.

## **FUNDING**

This study will be submitted for funding to the Australian and New Zealand College of Anaesthesia.

## **PUBLICATIONS**

The study will be published in the name of the of the study investigators. The chief investigator will be listed as the first author and other members of the management committee will be listed alphabetically. Funding bodies will be acknowledged in the publication

